## 5. Eligibility

### 5.1 Inclusion Criteria:

- Adult patients (> 18 years)
- CT or MRI proven acute ischemic (AIS) or hemorrhagic stroke (ICH) within 72h after onset of symptoms
- Severe hemiparesis (medical research council scale for muscle strength  $\leq 2$ )
- premorbid modified Rankin Scale (mRS)  $\leq 3$
- maximum National Institute of Health Stroke Scale Score (NIHSS) 25
- Voluntary written consent by the patient

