## 10. Outcome Assessments

### 10.1 Detailed description of assessment tools

#### *(i) Trunc Control Test (TCT)* 

The TCT examines 4 items of axial movements:

- 1) rolling from a supine position to the weak side;
- 2) rolling from a supine position to the strong side;
- 3) sitting up from a lying-down position; and
- 4) sitting in a balanced position on the edge of the bed with feet off the ground for 30 seconds.

For each item can be scored 0, 12 or 25 points:

- 0= unable to perform movement without assistance;
- 12= able to perform movement, but in an abnormal style (Examples: pulls on bed clothes or monkey pole, or uses arms to steady self when sitting);
- 25= able to complete movement normally.

For the sitting balance item, a patient scores 12 if he needs to touch anything with his hands to stay upright, and 0 if he is unable to stay up (by any means) for 30 seconds. The TCT score is the sum of the scores obtained on the four tests and ranges from 0 (minimum) to 100 (maximum and indicating better performance). The examiner's score must relate solely to the performance during the test.

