## **11 Sample size and statistical analysis plan:**

### 11.1 Sample size

This is a pilot trial. Vojta therapy has never been investigated in stroke patients. A sample size calculation for this pilot trial was not feasible, because desired parameters, as the estimated effect size or the standart deviation due to missing prior information or data in the literature could not be estimated. For feasability reasons we choose a sample size of 40 subjects (20 in each group) in order to complete recruitment in this monocentric trial within one to 1,5 years.

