### 11.2 Statistical analysis plan

We plan an intention to treat analysis. For the primary endpoint (difference of scores in trunc control test between day 9 and baseline) an increase of 12 points (=12%) on the scale of the TCT was predefined as a meaningful difference pragmatically, due to lack of data in the literature, because an improvement of 12 points in the TCT indicates a clinical relevant improvement of self-dependence (i.e. no more need of an auxiliary person, no more need for an adjuvant as edge of bed for moving). Normal distribution of the variables will be tested by the Shapiro-Wilk-test. For the primary endpoint we assume non-Gaussian distribution and we plan an analysis of variance with the non-parametric Mann–Whitney-U-test. The primary endpoint (difference of scores in trunc control test between day 9 and baseline) will be tested concerning the influencing factors a priori known to potentially affect outcome (age, sex, NIHSS > or <10 at baseline; stroke site, thrombolysis and thrombectomy) to test whether they affected the treatment. Complications occurring between baseline and day 9 will be analyzed with the exact Fisher Test. An interim analysis is not planned. We have not defined any discontinuation criteria. Statistical analysis will be made by the principal investigator with support of a statistical institute.

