### Acute stroke therapy:

- Treatment with recombinant tissue plasminogen activator and thrombectomy before randomisation are allowed.
- Surgical procedures (i.e. external ventricle drainage) before randomisation are allowed. Subjects must be able to sign the informed consent and to understand physiotherapeutic challenges.
- In case of deterioration with transfer to the intermediate care unit treatment will be continued there. If treatment or testing is not feasible (i.e. due to ventilation), testing should be performed one day later, if still within timeframe, otherwise testing should be cancelled. The final testing (visit 3) should then be performed as soon as the patient is testable again (if timeframe >day 10), even if he did not receive 7 treatment sessions in total.

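### The six-factor check in Section 11.2 has an unclear purpose, an NIHSS split with no place for a score of 10 and no stroke-type factor, and is uninformative about effect modification at N = 40

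*Protocol*

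**What the plan says.** Section 11.2 takes the change in TCT from baseline to day 9 as the primary endpoint and compares the arms with a Mann-Whitney test, assuming a non-Gaussian distribution. It then lists the factors against which this endpoint will be tested, and why: "age, sex, NIHSS > or <10 at baseline; stroke site, thrombolysis and thrombectomy) to test whether they affected the treatment". The opening of that sentence describes them as factors already known to have a possible influence on outcome. No method is named for this check. The yardstick for the endpoint is given just before: "an increase of 12 points (=12%) on the scale of the TCT was predefined as a meaningful difference pragmatically".

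Other parts of the protocol bear on the factors:

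- Section 5.1 admits both stroke types: "CT or MRI proven acute ischemic (AIS) or hemorrhagic stroke (ICH) within 72h after onset of symptoms". It caps the NIHSS at 25 and sets no minimum.
- Section 14 says of acute treatment: "Treatment with recombinant tissue plasminogen activator and thrombectomy before randomisation are allowed". It does not say how these treatments are coded as factors in patients with haemorrhage.
- Section 11.1 fixes the size for feasibility, 20 patients per arm, and states that "A sample size calculation for this pilot trial was not feasible".
- Section 6 gives up stratification by stroke severity because the sample is small.

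**The concern.** Three features of the sentence need attention.

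1. **Purpose.** A factor that influences outcome is prognostic and is best used to adjust the treatment comparison. A factor that changes the treatment effect is an effect modifier and calls for a treatment-by-factor interaction. The sentence starts with the first idea and ends with wording that reads as the second. The two lead to different analyses and different conclusions.
2. **Definition of the factors.** A baseline NIHSS of 10 is neither above nor below 10. Section 10.1 does not settle the matter, because 10 lies well inside its band of 5 to 14. Stroke type is absent from the list, while two treatments likely to be tied to stroke type are on it.
3. **Information.** If the check is about effect modification, 40 patients give very imprecise answers. A chance result in one subgroup could be read as showing where Vojta therapy works, and a true difference would probably be missed. Meanwhile the baseline measurements, which could sharpen the main comparison, are not used for that.

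**Working it through.** The protocol has no calculation to reproduce. Its sample size carries no power, and on the usual inputs it says that "the estimated effect size or the standart deviation due to missing prior information or data in the literature could not be estimated".

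**Inputs from the protocol:** 20 patients per arm; six factors; a meaningful difference of 12 points on a scale that "ranges from 0 (minimum) to 100 (maximum and indicating better performance".

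**Assumed, because not stated:** two-sided 5% level; SD of the TCT change 10 to 30 points; normal approximation; each factor distributed alike in both arms.

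**Interaction.** Let f be the share of patients in one level of a two-level factor. The difference between the two subgroup treatment effects has

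SE = SD × √(2/(20f) + 2/(20(1−f))).

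For f = 0.5 there are 10 patients per cell and SE = SD × √(4/10) = 0.632 SD. The interaction detectable with 80% power is (1.96 + 0.84) × SE = 1.77 SD.

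| SD (assumed) | SE | Half-width of 95% CI | Detectable at 80% power | Power for 12 points |
|---|---|---|---|---|
| 10 | 6.3 | 12.4 | 17.7 | 48% |
| 15 | 9.5 | 18.6 | 26.6 | 24% |
| 20 | 12.6 | 24.8 | 35.4 | 16% |
| 25 | 15.8 | 31.0 | 44.3 | 12% |
| 30 | 19.0 | 37.2 | 53.2 | 10% |

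Uneven factors do worse. The detectable interaction is 1.93 SD at a 30:70 split, 2.21 SD at 20:80 and 2.95 SD at 10:90. For comparison, the main effect has SE = SD × √(2/20) = 0.316 SD and a detectable difference of 0.89 SD, half that of an evenly split interaction. For 80% power on a 12-point interaction with an even split, the total sample would be about 88 (SD 10), 200 (SD 15), 352 (SD 20) or 792 (SD 30).

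**Multiplicity.** If the six factors were tested separately and independently at 5%, the chance of at least one false positive would be 1 − 0.95⁶ = 0.265. Correlation between the factors would lower this.

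**Score of exactly 10.** If 3% to 10% of patients have this score (assumed), the expected number is 40 × 0.03 = 1.2 to 40 × 0.10 = 4. The chance of at least one such patient is 1 − 0.97⁴⁰ = 70% to 1 − 0.90⁴⁰ = 99%.

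**Stroke type.** Suppose thrombolysis and thrombectomy are given mainly in ischaemic stroke (assumed; the protocol does not say so). A yes/no factor over all patients then compares treated ischaemic stroke with a mixture of untreated ischaemic stroke and haemorrhage. Any contrast could reflect stroke type instead of acute treatment, and the listed factors offer no way to separate the two.

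**Chance imbalance.** Without stratification, the between-arm difference in the mean of a baseline covariate has SE √(2/20) = 0.32 of that covariate's SD, so in about one trial in three it exceeds 0.32 SD in either direction. The unadjusted comparison does not correct for this.

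**The case against.** The strongest reply is that much of the criticism depends on how the sentence is read.

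- A reader might infer that patients scoring 10 are dropped. The protocol does not say so. It plans an intention-to-treat analysis, and the primary comparison does not use NIHSS. The gap affects only the secondary grouping, where no rule is given.
- A reader might infer that haemorrhages are coded as not thrombolysed. That is also not stated, and a more detailed plan could restrict these factors to ischaemic stroke. What is fact is that both stroke types are enrolled and stroke type is not on the list.
- A reader might infer six separate tests, or the Mann-Whitney test as the method for the factor check. Neither is stated. One model with six terms would fit the wording, and the rank test is named only for the comparison of arms. The 26% is therefore conditional.
- If the check is meant as prognostic, the interaction calculation does not apply to it.
- Low power for interactions misstates nothing in a declared pilot whose size was set for feasibility.

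All of this stands, and it limits the point. It does not remove it: the protocol itself fixes the factors, the split and the stated aim, and these need correcting on either reading. A remedy that simply replaced the rank test with a Gaussian model would also conflict with the stated distributional assumption, so the adjusted analysis has to respect that.

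**Conclusion.** The point holds in a limited form. On the text alone, the purpose of the check is worded in two incompatible ways, an eligible NIHSS of 10 has no category, and stroke type is not a factor. The mixing of acute treatment with stroke type is conditional: it follows if those factors are applied as yes/no to all patients.

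As a study of effect modification, the check is uninformative at N = 40. An evenly split factor needs an interaction of about 1.8 SD for 80% power, 27 to 53 points at an assumed SD of 15 to 30. Even at SD 10 the requirement is 17.7 points, and power for 12 points stays below 50%. These figures rest on the assumed level, SD and balance. The 12 points are the protocol's yardstick for the TCT change, used here only for scale.

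The documents do not support the stronger conclusions that patients are lost from the primary analysis or that the sample size is in error. The matter is one of definition and of wasted information, and it can be corrected cheaply.

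**What to change.** In Section 11.2:

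1. State one purpose for the factors, namely prognostic.
2. Beside the planned Mann-Whitney test, add a baseline-adjusted analysis of the treatment difference in TCT, with baseline TCT and continuous NIHSS as covariates. To fit the non-Gaussian assumption, use a rank-based or otherwise robust form, for example rank analysis of covariance, or a linear model with a bootstrap interval.
3. Define any displayed NIHSS groups as below 10 and 10 or above.
4. Add stroke type (ischaemic or haemorrhagic) as a factor, and examine thrombolysis and thrombectomy within ischaemic stroke.
5. Report treatment differences by factor as exploratory estimates with 95% confidence intervals and no significance claims.

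The cost is a few sentences, a little more analysis work and one more model assumption. No new data are needed: Section 9 already has TCT and NIHSS recorded before the first treatment, and imaging-confirmed stroke type is part of eligibility.

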### **8.3 Safety Outcomes**

All adverse events and serious adverse events are recorded and assessed by the investigators throughout the trial until day 90 according to standard definitions. All deaths until 3 months and the serious adverse during the hospital stay will be evaluated and forwarded to a medical expert for assessment of relatedness to the study treatment.

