## 9. Timeframes for Visits Outcome Measures

- Randomisation: Maximum 72h after stroke onset
  - Test 1: on day 2 after admission to hospital (+/- 1 day)
  - Test 2: on day 5 after admission to hospital (+/- 1 day)
  - Test 3: on day 9 after admission to hospital (+/- 1 day)
  - Test 4: on day 90 after stroke onset (+/- 5 days)
- The trunc control test (TCT) will be assessed at day 2 after admission to hospital before the first treatment (baseline), at day 5 and day 9 after treatment.
  - The National Institutes of Health Stroke Scale (NIHSS) will be assessed at day 2 after admission to hospital before the first treatment (baseline) and at day 9 after treatment.
  - The Catherine Bergego Scale (CBS) and the Motor Evaluation Scale for Upper Extremity in Stroke Patients (MESUPES) will be assessed at day 2, day 5 and day 9 after admission before and after treatment.
  - The modified Rankin Scale (mRS) and the Barthel Index (BI) will be assessed at day 2 after admission to hospital before the first treatment (baseline), at day 9 after treatment and at day 90 after stroke onset via a phone interview.
  - Investigators will record the occurrence of any serious adverse event and other safety outcomes that occur during hospital admission up to day 90.

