**Table 2: trial schedule**

|                                    | Screening visit | Baseline visit | Follow up visits |              |              |               |
|------------------------------------|-----------------|----------------|------------------|--------------|--------------|---------------|
| Procedures                  | 1) Screening    | 2) Enrollement | 3) Test 1        | 4) Test 2    | 5) Test 3    | 6) Test 4     |
|                                    | day 1-3         | day 1-3        | day 2(+/-1)      | day 5 (+/-1) | day 9 (+/-1) | day 90 (+/-5) |
| Check inclusion/exclusion criteria | X               | X              |                  |              |              |               |
| Randomisation                      |                 | X              |                  |              |              |               |
| Informed consent                   |                 | X              |                  |              |              |               |
| Clinical examination               | X               | X              | X                | X            | X            |               |
| Medical history                    | X               |                |                  |              |              |               |
| Demographic data                   | X               |                |                  |              |              |               |
| Concomitant medication             |                 | X              |                  |              | X            | X             |
| Adverse events                     |                 | X              | X                | X            | X            | X             |
| Imaging (CCT/MRI)                  | X               |                |                  |              |              |               |
| NIHSS                              | X               |                | X                |              | X            |               |
| mRS                                | Premorbid-mRS   |                | X                |              | X            | X             |
| CBS (5+6) (neglect test)           |                 |                | X                | X            | X            |               |
| MESUPES arm (1-4)                  |                 |                | X                | X            | X            |               |

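### Section 11.2 compares complications between arms only to day 9, while adverse events are recorded to day 90; non-fatal events after day 9 have no stated by-arm comparison

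*Protocol*

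**What the plan says.** **Recording.** Section 8.3 states: "All adverse events and serious adverse events are recorded and assessed by the investigators throughout the trial until day 90 according to standard definitions". Section 9 says much the same: "Investigators will record the occurrence of any serious adverse event and other safety outcomes that occur during hospital admission up to day 90". Table 2 marks adverse events at enrolment and at Tests 1, 2, 3 and 4, and Test 4 is the day-90 contact.

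**Comparison of arms.** Section 11.2, which is headed as the statistical analysis plan, contains one sentence on safety: "Complications occurring between baseline and day 9 will be analyzed with the exact Fisher Test". It does not tie complications to the AEs and SAEs of Section 8.3.

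**Individual review.** Section 8.3 adds: "All deaths until 3 months and the serious adverse during the hospital stay will be evaluated and forwarded to a medical expert". The purpose is an assessment of relatedness to study treatment.

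**Deaths.** Section 10.1 gives death a score of 6 on the mRS. The change in mRS from baseline to day 90 is secondary outcome (v) in Section 8.2.

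**The concern.** The document sets three safety windows that do not match: recording to day 90, expert review of deaths to 3 months but of SAEs only in hospital, and a test of the arms that stops at day 9. A non-fatal AE or SAE after day 9 is recorded and assessed by the investigators, but no stated analysis compares it between arms. If it occurs after discharge, it is not forwarded to the expert either.

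Section 8.2 gives day 9 as the average stay before transfer to rehabilitation, so for many patients the two gaps open at about the same time.

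The stake is what the pilot can report. Section 11.1 says that Vojta therapy has not been studied before in stroke patients and sets the sample size by feasibility. A description of safety by randomised arm, over the period actually observed, is one of the more useful things such a trial can deliver. The plan as written delivers it for the first days only.

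**Working it through.** The protocol states no computed safety figure, so there is none to reproduce. Three checks were made.

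**1. Share of follow-up time outside the tested window**

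Inputs from Section 9: Test 1 (baseline) on day b = 2 ± 1 and Test 3 on day c = 9 ± 1, both after admission; Test 4 on day e = 90 ± 5 after onset. The lag L from onset to admission is not given. It is assumed to be 0 to 3 days, since randomisation must fall within 72 hours of onset.

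Share outside = 1 − (c − b) / (e − L − b)

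| b | c | e | L | Calculation | Share outside |
|---|---|---|---|---|---|
| 2 | 9 | 90 | 0 | 1 − 7/88 | 92.0% |
| 2 | 9 | 90 | 3 | 1 − 7/85 | 91.8% |
| 1 | 10 | 85 | 3 | 1 − 9/81 | 88.9% |
| 3 | 8 | 95 | 0 | 1 − 5/92 | 94.6% |

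**2. Share of events outside the window**

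The protocol gives no event rates. Assume a cumulative hazard proportional to t^k, counted from baseline, where k = 1 is a constant hazard and smaller k means more events early. Then the share after day 9 = 1 − (7/88)^k.

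| k | Share of events after day 9 |
|---|---|
| 1 | 92% |
| 0.5 | 72% |
| 0.3 | 53% |
| 0.2 | 40% |

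The share is one half at k = ln 0.5 / ln(7/88) = 0.27. Whether most events fall after day 9 therefore depends on an assumption that the protocol cannot settle.

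**3. What any comparison could show with 20 per arm** (two-sided 5% level assumed)

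- Fisher's exact test: 4 v 0 gives p = 0.106; 5 v 0 gives p = 0.047; 6 v 1 gives p = 0.091; 7 v 1 gives p = 0.044.
- Exact power at assumed rates: 0.24 for 10% v 30%, 0.49 for 10% v 40%, 0.74 for 10% v 50%.
- Upper exact 95% limit for 0 of 20: 1 − 0.025^(1/20) = 16.8%.

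These figures depend on n = 20 and not on the length of the window. They apply at day 9 and at day 90 alike, so a day-90 comparison should be descriptive.

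**The case against.** The strongest defence is that day 9 follows the treatment. Section 12.1 schedules seven daily sessions before the day-9 test, so the Fisher test covers roughly the treatment period, which is a reasonable comparison for a short physical therapy. Later data are also thinner: after Test 3 the only scheduled contact is the day-90 telephone call. Both points stand. They are reasons to keep the day-9 test and to read later results with care, but not to leave recorded events unsummarised.

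A second defence is that Section 11.2 does not say the day-9 test is the only safety analysis, and a separate SAP may add tables. That is fair as far as it goes. But Section 11.2 fixes a short window and is not silent on the matter, so it would need reconciling with any such SAP.

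A reader might also infer four stronger things that the protocol does not support:

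- *Most safety events go uncompared.* This is shown for time only, not for events (check 2).
- *Nothing recorded after day 9 enters any planned outcome or review.* Deaths enter the day-90 mRS. Deaths to 3 months and all in-hospital SAEs, including those after day 9, receive expert review.
- *The sickest patients are still on study treatment after the window closes.* Section 14 says: "In case of deterioration with transfer to the intermediate care unit treatment will be continued there". That concerns where treatment takes place. The section also allows late final testing with fewer than seven sessions. It does not say that sessions run past day 9.
- *The short window makes a non-significant result almost certain, or favours a claim of no difference.* No event rates are given, the limits in check 3 come from the sample size, and the protocol plans no such claim.

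**Conclusion.** The mismatch stands in the text. The only between-arm safety analysis that Section 11.2 names ends at day 9, against recording to day 90. Non-fatal AEs and SAEs after day 9 have no stated by-arm comparison, and SAEs after discharge are outside the relatedness review. Deaths to day 90 count only within the mRS, where they are mixed with disability and not shown as deaths.

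In size, about 92% of follow-up time is outside the tested window (89% to 95%, given the visit windows and an assumed lag of 0 to 3 days). The share of events is unknown.

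The point does not touch the primary endpoint. With 20 per arm, a longer window will not yield a confirmatory safety result. The gain is a complete description by arm, at little cost. The verdict rests on Section 11.2 as shown; a SAP that already gives by-arm tables to day 90 would reduce it to a matter of aligning the wording.

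**What to change.** 1. **Section 11.2, keep:** the Fisher test as the on-treatment comparison, with its window running to each patient's actual Test 3 date, since Test 3 may fall on day 8 to 10 or later after deterioration. State how complications relate to the AEs and SAEs of Section 8.3.
2. **Section 11.2, add:** a by-arm summary from randomisation to day 90 of patients with at least one AE, patients with at least one SAE, and deaths. Give each as a risk difference with an exact 95% confidence interval, and label the table descriptive because 20 per arm gives low power.
3. **Section 8.3, reconcile:** the window for evaluating SAEs (hospital stay) with the window for recording them (day 90), so that the handling of SAEs after discharge is explicit.

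**Cost.** A few sentences and one more table on data the protocol already collects, plus some further SAE reviews if the evaluation window is lengthened. Two limits should be stated beside the results. Events after discharge rest on a single scheduled telephone contact, so they are less completely ascertained than in-hospital events. A window ending at the actual Test 3 date also varies in length between patients, so the day of Test 3 should be shown by arm.
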